| Exploratory Objectives:                                                                                                                                                                                                                                                                                                                                                                                                                                                                                                                                           | Exploratory Endpoints:                                                                                                                                                                                                                                                                                    |
| 
 
To evaluate PD effects of KAT6A/6B inhibition following PF-07248144 treatment as a single agent (Part 2A) and in combination with fulvestrant (2B) [REDACTED].
 
To explore potential predictive biomarkers of clinical response, mechanisms of action, and mechanisms of resistance as a single agent (Part 2A) and in combination with fulvestrant (2B) [REDACTED].
 
To evaluate the metabolic profiling of PF-07248144 in a subset of participants in Part 2A (approximately 6 participants).
 
 | 
 
Changes from [REDACTED] in [REDACTED].
 
[REDACTED].
 
[REDACTED] analyses of [REDACTED] and their relationship to clinical response.
 
[REDACTED] that may be related to response or resistance to treatment.
 
[REDACTED]
 
 |

## 4. STUDY DESIGN

### 4.1. Overall Design

This is an open-label, multi-center Phase 1 study in adult participants to evaluate safety, tolerability, PK, and PD of PF-07248144 in locally advanced or metastatic selected solid tumors (ER+HER2- breast cancer, CRPC, or NSCLC) and early signs of clinical activity of PF-07248144 as a single agent and in combination in ER+HER2- breast cancer. The overall study design is depicted in the schema ([Section 1.2](#)).

**Part 1** dose escalation consists of: Part 1A, Part 1B [REDACTED]

**Part 1A** contains dose escalation as monotherapy in participants with locally advanced or metastatic ER+HER2- breast cancer, CRPC, or NSCLC that are resistant or intolerant to standard therapy or for whom no standard therapy is available, to determine the MTD and select the RDE. Participants will receive escalating doses of PF-07248144. BLRM guided by EWOC principle will be used to guide dose escalation process and determine the MTD. [REDACTED] Maximum allowable PF-07248144 dose increment is 100% unless in circumstance defined in [Section 4.3.3](#). DLT will be assessed during Cycle 1 (the first 28 days with the inclusion of C2D1 laboratory assessments). Each dose level group will be approximately 3 participants, with at least 1 DLT-evaluable participant per cohort in the first 2 cohorts and at least 2 DLT evaluable participants per dose level group in the remaining cohorts for Part 1A. Per BLRM design, expanding additional

participants at lower dose levels is allowed to assess safety. Additional dosing frequency such as intermittent dosing may be considered if supported by emerging clinical data.

**In Part 1B**, PF-07248144 in combination with fulvestrant, will be evaluated for dose finding in participants with locally advanced or metastatic ER+HER2- breast cancer (2L+) who have progressed after at least 1 line of treatment with an endocrine therapy and CDK4/6 inhibitor to determine the MTD and RDE for this combination. The definitions of RDE and RP2D are provided in [Section 4.3.7](#). Combination RDE may be different from monotherapy RDE due to potential toxicity overlap or drug-drug interaction.

[REDACTED]

[REDACTED]

[REDACTED] Treatment will continue until PD, unacceptable toxicity, or participant refusal, whichever occurs first.

BLRM specifically developed for double and triple combinations will be used for dose finding in Part 1B, [REDACTED] PF-07248144 may start at 1 dose level below the monotherapy RDE (RDE-1) with fixed doses of fulvestrant [REDACTED]. The definitions of MTD and RDE are provided in [Section 4.3.6](#) and [4.3.7](#). In addition, depending on the safety findings in Part 1A, and whether significant overlapping toxicities are expected in combination, the starting dose of PF-07248144 in combination can be further modified to a lower dose. The sponsor may choose to advance a lower dose to start the combination dose finding Part 1B, [REDACTED] prior to the monotherapy MTD being reached. This decision will be made based on emerging preliminary safety, PK, PD, and/or activity data during Part 1A. At least 2 DLT evaluable participants will be required for dose level groups in Part 1B, [REDACTED].

After the determination of the monotherapy expansion RDE in Part 1A, PF-07248144 will be evaluated in a dose expansion cohort as a monotherapy in locally advanced or metastatic ER+HER2- breast cancer (2L+) who have progressed after at least 1 prior line of CDK4/6 inhibitor and 1 line of endocrine therapy (Part 2A). The definitions of RDE and RP2D are provided in [Section 4.3.7](#). [REDACTED]

A food effect assessment will take place in a subset of participants (approximately 6) in Part 2A. Each participant will serve as his/her own control in which PF-07248144 will be

administered in the morning under “fed conditions” on Cycle 1 Day -7 and under “fasted” conditions on Cycle 1 Day 1. Additional details are provided in [Section 4.3.8](#).

PK and metabolite profiling in both urine and blood will be assessed in a subset of participants (approximately 6) in Part 2A. Both urine and blood samples should be collected from the same participants at screening and on Cycle 1 Day 15 ([Sections 8.5.2](#) and [8.5.3](#)).

After determination of the combination RDE from Part 1B, PF-07248144 in combination with fulvestrant will be evaluated in a dose-expansion combination cohort in participants with advanced or metastatic 2-4L ER+HER2- breast cancer whose disease has progressed after at least 1 prior line of a CDK4/6 inhibitor and at least 1 prior line of endocrine therapy and who must not have received more than 3 lines of systemic therapies in advanced or metastatic setting (Part 2B). Paired [REDACTED]  
[REDACTED]

Furthermore, to better characterize safety, PK and potential efficacy, each dose expansion may investigate more than one dose level(s) of the study intervention(s) in up to an additional 30 participants. The dose levels to be evaluated will be informed by available data from dose escalation (including safety, PK/PD, and activity) and will not exceed the monotherapy MTD unless the observed exposure in combination significantly lower than monotherapy.

[REDACTED] the MTD and/or RDE based on emerging and available preliminary clinical data, including safety/tolerability, laboratory, PK, and PD findings. [REDACTED] from the MTD and/or RDE of the QD/BID regimen and satisfying EWOC criteria. PF-07248144 [REDACTED], if indicated based on emerging clinical data.

### Number of Participants

The total number of participants is estimated to be approximately 140 to 200

**Part 1 Dose Escalation:** Approximately 70 participants will be enrolled in Part 1 including 25 to 30 participants in Part 1A, 6 to 9 participants in Part 1B, [REDACTED]

[REDACTED]

[REDACTED]

[REDACTED] n addition, [REDACTED] herefore, the use of a highly effective method of contraception is required (see [Appendix 4: Section 10.4](#)).

#### **4.2.2. Preclinical rationale for PF-07248144 (KAT6** [REDACTED]

KAT6A and KAT6B acetyltransferases are involved in regulation of fundamental cellular process including gene transcription, cellular senescence, tissue differentiation and stem cell maintenance. In ER+ breast cancer, KAT6A is a direct transcriptional regulator of ESR1 and promotes growth of ER+ breast cancer cells by driving ER signaling. KAT6A can also promote cell proliferation by upregulating MYC transcriptional programs along with inhibition of cellular senescence via the INK4A-ARF pathway. [REDACTED]

[REDACTED]

[REDACTED]

[REDACTED]

[REDACTED]

[REDACTED]

[REDACTED]

[REDACTED]

|            |            |            |            |            |            |            |
|------------|------------|------------|------------|------------|------------|------------|
| [REDACTED] | [REDACTED] | [REDACTED] | [REDACTED] | [REDACTED] | [REDACTED] | [REDACTED] |
| [REDACTED] | [REDACTED] | [REDACTED] | [REDACTED] | [REDACTED] | [REDACTED] | [REDACTED] |
| [REDACTED] | [REDACTED] | [REDACTED] | [REDACTED] | [REDACTED] | [REDACTED] | [REDACTED] |
| [REDACTED] | [REDACTED] | [REDACTED] | [REDACTED] | [REDACTED] | [REDACTED] | [REDACTED] |
| [REDACTED] | [REDACTED] | [REDACTED] | [REDACTED] | [REDACTED] | [REDACTED] | [REDACTED] |
| [REDACTED] | [REDACTED] | [REDACTED] | [REDACTED] | [REDACTED] | [REDACTED] | [REDACTED] |
| [REDACTED] | [REDACTED] | [REDACTED] | [REDACTED] | [REDACTED] | [REDACTED] | [REDACTED] |
| [REDACTED] | [REDACTED] | [REDACTED] | [REDACTED] | [REDACTED] | [REDACTED] | [REDACTED] |
| [REDACTED] | [REDACTED] | [REDACTED] | [REDACTED] | [REDACTED] | [REDACTED] | [REDACTED] |

[REDACTED]

[REDACTED]

[REDACTED]

[REDACTED]

[REDACTED]

PF-07248144 (current study C4551001) has demonstrated a tolerable safety profile with reversible and manageable hematological toxicities ([Section 2.2.4](#)).

3 DLTs were reported (G3 neutropenia) during dose escalation and all were resolved with dose modification. Grade  $\geq 3$  treatment-related AEs in more than one participant include: neutrophil count decreased/neutropenia in 17 participants (28.8%); anemia in 6 participants (10.2%) and white blood cell count decreased in 4 participants (6.8%).

The dosing regimen of 5 mg QD was identified as the RDE for monotherapy and fulvestrant combination. Encouraging clinical responses (eg, PRs) were observed in monotherapy and the fulvestrant combination in heavily pretreated ER+ HER2- breast cancer.

[REDACTED]

[REDACTED]

[REDACTED]

[REDACTED]

[REDACTED]

[REDACTED]

#### 4.2.4. Estrogen Receptor (ER) Positive Breast Cancer

Breast cancer is the most common noncutaneous cancer in women with over 275,000 new cases expected to be diagnosed in the US in 2020^23. Approximately 70-80% of new breast cancers express the estrogen and/or progesterone receptor. A more contemporary approach to treat ER-positive advanced or metastatic breast cancer involves combining novel agents with existing endocrine therapy to block pathways enabling partial or complete endocrine resistance.

Although patients with ER-positive tumors can benefit from hormonal therapy and CDK4/6 inhibitors, the majority of these women develop resistance to endocrine therapy at some point during treatment. Therefore, there is a high unmet medical need to develop novel agents.

Together, these data provide rationale for exploring potential application of PF-07248144 as monotherapy and in combination with standard of care agents in ER+HER2- breast cancer.

#### 4.2.5. Prostate Cancer

Prostate cancer is the most common cancer in American men (aside from skin malignancies). The American Cancer Society estimates that in the US in 2020 there will be 191,930 newly diagnosed cases of prostate cancer and over 33,000 prostate cancer-related deaths. The early stages of prostate cancer are localized to the prostate, often indolent in nature, and treatable by operative resection or radiotherapy. However, the majority of patients are at a high risk of disease recurrence; and, once metastatic, of disease progression. Prior to the recent approval of NHT (enzalutamide, abiraterone acetate/prednisone), the only approved therapies for CRPC were docetaxel, cabazitaxel and sipuleucel-T. The approval of NHTs in metastatic CRPC previously treated with docetaxel represented a therapeutic advance for these patients. Given this disease biology, there is high unmet medical need for new therapies to provide long-term disease control while offering a better quality of life with manageable side effect profiles. Preclinically, PF-07248144 has demonstrated potent cellular activity in prostate cancer models, thus providing rationale for exploring potential application of PF-07248144 in prostate cancer.

#### 4.2.6. NSCLC

The American Cancer Society estimates that there will be over 228,000 new cases of lung cancer diagnosed in the US in 2020, with over 135,000 deaths. About 80-85% of lung cancers are histologically classified as NSCLC, which includes 2 major sub-types: 1) non-squamous carcinoma (including adenocarcinoma, large-cell carcinoma [rare], and other

cell types) and 2) squamous cell (epidermoid) carcinoma. The 5-year survival rate of metastatic NSCLC is 4%. Pembrolizumab, an immune checkpoint inhibitor, is approved either as a monotherapy or in combination with chemotherapy for first-line treatment of NSCLC patients without a targetable oncogene driver (eg, EGFR, ALK, ROS1). Treatment options are limited once a patient progresses on a PD-1/PD-L1 inhibitor (eg docetaxel, ramucirumab), thus there is still a high unmet medical need to find novel therapies to address this patient population. Preclinically, analysis of functional genomics data [REDACTED]

[REDACTED] providing rationale for potential exploration of PF-07248144 in NSCLC based on emerging data.

#### 4.2.7. Background and Rationale for Biomarker Assessment

The objectives of the biomarker assessments in this study are: 1) to assess the pharmacodynamic effects of PF-07248144 as monotherapy, in combination with ET, [REDACTED] by characterizing modulation of PD biomarkers in both tumor tissue and peripheral blood. These [REDACTED] in tumor [REDACTED] and changes [REDACTED]; and 2) to explore potential predictive biomarker(s) and mechanisms of resistance to PF-07248144 therapy, when used as either a single agent, or in combination therapy.

The biomarker assessments may contribute to confirming target engagement, determining PD effects of PF-07248144, identifying those participants who are most likely to benefit from treatment, and identify potential resistance mechanisms to PF-07248144. These assessments may also be used to correlate the PD effect with PK parameters of PF-07248144, and to aid the selection of the RDE of PF-07248144. [REDACTED] as described in the [SoA](#) and the Laboratory Manual.

Banked Biospecimens will be collected and stored for further analyses which may, for example, provide greater understanding of the study intervention.

#### 4.3. Justification for Dose

Doses presented are projected based on nonclinical data and may be modified based on emerging safety, tolerability, and PK data.

##### 4.3.1. PF-07248144 Starting Dose for Monotherapy Dose Escalation

The selection of the starting dose for this FIH study is based on the preclinical toxicology results in accordance with ICH S9 Guidance entitled “Nonclinical Evaluation for Anticancer Pharmaceuticals”.

The starting dose for [REDACTED]

[REDACTED]

The predicted apparent half-life by the PBPK modeling is approximately 12 hours at the dose of 8 mg, suggesting a QD dosing regimen. For additional information, please see the Investigator Brochure (IB).

[REDACTED]

In summary, [REDACTED]

|  |  |  |  |  |  |  |  |  |  |
|--|--|--|--|--|--|--|--|--|--|
|  |  |  |  |  |  |  |  |  |  |
|  |  |  |  |  |  |  |  |  |  |

[REDACTED]

|  |  |  |  |  |  |
|--|--|--|--|--|--|
|  |  |  |  |  |  |
|  |  |  |  |  |  |
|  |  |  |  |  |  |
|  |  |  |  |  |  |
|  |  |  |  |  |  |
|  |  |  |  |  |  |

|  |  |  |  |  |  |
|--|--|--|--|--|--|
|  |  |  |  |  |  |
|  |  |  |  |  |  |
|  |  |  |  |  |  |
|  |  |  |  |  |  |
|  |  |  |  |  |  |
|  |  |  |  |  |  |

#### 4.3.3. Dose Increment

In Part 1A, the maximum allowable dose increment of PF-07248144 is 100%. However, a maximum allowable dose-increment >100% (up to 150%) may be considered based on the emerging PK data.

[figure not shown]

Review of single and multiple dose PK data, together with Cycle 1 safety observations, from all available participants will be conducted prior to determining whether a >100% (up to 150%) maximum allowable dose increment will be implemented. This decision should be discussed and approved by both investigator and sponsor.

For combination dose escalation in Parts 1B, a maximum allowable dose increment of PF-0728144 ) to a dose level already determined to be safe as monotherapy may be allowed. For instance, a dose increment from 2 mg QD to 5 mg QD for PF-07248144 may be considered as guided by the BLRM with EWOC principle.

The dose of PF-07248144 in combination, may not exceed the monotherapy MTD/RDE , unless emerging clinical data suggest combination may significantly reduce exposure in

which case further dose increase may be considered based on the consensus of investigators and Sponsor.

Not all the dose levels explored in the monotherapy studies may be tested in combination. Intermediate doses may be evaluated based on emerging clinical safety and PK/PD data.

#### 4.3.4. Criteria for Dose Escalation

BLRM guided by the EWOC principle will be used in dose escalation. A traditional 2 -parameter BLRM will be used to model the dose/DLT relationship of PF-07248144 monotherapy and, BLRMs developed specifically for combinations will be used to model the dose/DLT relationship of PF-07248144 given in combination with fulvestrant (Part 1B).

Using DLT data at all tested dose levels and pre-specified prior distribution of model parameters, the posterior distribution for probability of having a DLT will be calculated for all dose levels and dose recommendations using EWOC will be provided.

Dose recommendation will be based on the probability that the true DLT rate for each dose lies in 1 of the following categories:

|                  |              |
|------------------|--------------|
| Under-dosing:    | [0, 0.16]    |
| Targeted dosing: | [0.16, 0.33] |
| Overdosing:      | [0.33, 1]    |

A dose may only be used for newly enrolled participants if it satisfies EWOC criteria: the risk of excessive toxicity (overdosing) at that dose is less than 25%.

The maximum allowable PF-07248144 dose increment is 100% except as defined in [Section 4.3.3](#).

Dose escalation will stop when stopping criteria are met (see [Section 9.4.1.1](#)). In an unlikely situation of observing DLT(s) at the starting dose level, lower dose levels might be considered. The dose level will be recommended by BLRM in such a way that EWOC criteria are fulfilled.

Intra-participant dose escalation will not be permitted in this study. In case of change of the dosing regimen, DLT data accumulated during the dose escalation with the original regimen might be used to form a prior for further BLRM analysis. Details about derivation of this prior using Meta-Analytic-Predictive (MAP) approach can be found in [Section 10.9](#).

#### 4.3.5. Dose Limiting Toxicity Definition

DLT evaluable: A participant is classified as DLT evaluable if the participant experiences a DLT or if the participant otherwise in the absence of a DLT receives at least 75% of the planned doses of PF-07248144 and has received all scheduled safety assessments during the

DLT observation period. If a participant fails to meet these criteria, the participant is classified as not DLT-evaluable and may be replaced.

DLT observation period: For the purpose of dose escalation, the DLT observation period for monotherapy dose escalation (Part 1A) and combination dose escalation (Part 1B, [REDACTED]) will be the first cycle of treatment (within 28 days of the first dose) with inclusion of the Cycle 2 Day 1 (Day 29) laboratory assessments in each participant.

Significant AEs considered to be related to the study intervention or treatment under investigation that occur after the DLT observation period will be reviewed in the context of all safety data available. That review may result in re-evaluation of the dosing level or regimen.

Severity of AEs will be graded according to CTCAE version 5.0. For the purpose of dose escalation/finding, any of the following AEs occurring in the first cycle of treatment (28 days) which are attributable to one, the other, or all agents in the combination will be classified as DLTs:

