| PF-07248144 administration
p                       |                                                                      | Orally, QD continuously.                                                  |       |        |        |                      |        |                               |           |                  |                                                                           |
| [REDACTED]                                                       |                                                                      | [REDACTED]                                                                |       |        |        |                      |        |                               |           |                  |                                                                           |
| fulvestrant administration r
(Parts 1B [REDACTED]) |                                                                      | Intramuscularly, 500 mg on C1D1, C1D15, C2D1 and once monthly thereafter. |       |        |        |                      |        |                               |           |                  |                                                                           |
| [REDACTED]                                                       |                                                                      | [REDACTED]                                                                |       |        |        |                      |        |                               |           |                  |                                                                           |
| [REDACTED]                                                       |                                                                      | [REDACTED]                                                                |       |        |        |                      |        |                               |           |                  |                                                                           |

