#### **Non-Hematologic Dose-Limiting Toxicities:**

Any Grade  $\geq 3$  non-hematologic possibly treatment related AE is a DLTs with the following clarifications:

- Grade  $\geq 3$  nausea, vomiting, or diarrhea lasting  $\geq 3$  days despite adequate antiemetic and other supportive care is a DLT.
- Grade  $\geq 3$  fatigue lasting  $\geq 7$  days is a DLT.

- Confirmed DILI meeting Hy's law criteria is a DLT.
- For participants with Grade 2 hepatic transaminase or alkaline phosphatase levels at baseline as a result of liver metastasis or bone metastasis, AST or ALT >10 x ULN or AST or ALT >5 x ULN for  $\geq 14$  days will be considered a DLT
- Clinically important or persistent toxicities (eg, toxicities responsible for significant dose delay) that are not included in the above criteria may also be considered a DLT following review by the investigators and the Sponsor. All DLTs need to represent a clinically significant shift from baseline.
- Grade  $\geq 3$  QTc prolongation is a DLT.
- Grade  $\geq 3$  anaphylaxis is a DLT.

Any toxicity causing greater than 2 weeks of dose delay of either PF-07248144 [REDACTED] is a DLT. In addition, any Grade 5 AE (death) not clearly due to either the underlying disease or other etiologies is a DLT. *Note:* Participants deriving clinical benefit from study intervention who experience a DLT may continue on study at a reduced dose following recovery of the AE to Grade 1 or baseline, only after discussion between the Investigator and Sponsor.

Any dose reduction of either PF-07248144 [REDACTED] due to a treatment-related AE (per protocol) during the first 28 days will be qualified as participant experiencing DLT.

The following AEs will not be adjudicated as DLTs:

- Isolated Grade 3 laboratory abnormalities that are not associated with clinical sequelae and are corrected or resolved to Grade 1 or baseline with supplementation/appropriate management within 72 hours of their onset.

Adverse events consistent with the definition of a DLT observed after the DLT observation period may also be considered in dose escalation decisions and the final determination of the MTD/RDE as monotherapy and in combination.

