**Sensitivity Analysis:**

To mitigate the risk of dichotomizing and misclassifying DLTs, a sensitivity analysis that uses weighted DLT/AE data (in equivocal cases) into the BLRM model estimation will also be performed. If all the investigators and the sponsor agree on the equivocal DLT/AE data, the DLT weighting approach could be the primary dose escalation method. See [Appendix 9 \(Section 10.9\)](#) for more details.

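### Missing 8 to 14 Cycle 1 doses for toxicity need not be a DLT, yet makes the participant replaceable under 4.3.5, and 9.3 leaves open how that participant enters the MTD data

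*Protocol*

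**What the plan says.** Protocol 4.3.5 gives two ways to be DLT-evaluable: have a DLT or, without one, be a participant who "receives at least 75% of the planned doses of PF-07248144 and has received all scheduled safety assessments during the" DLT observation period. Anyone else fails the rule: "the participant is classified as not DLT-evaluable and may be replaced". Nothing in the rule asks why doses were missed. The observation period "will be the first cycle of treatment (within 28 days of the first dose"), plus the Day 29 laboratory results. Table 1 gives the PF-07248144 schedule as "Orally, QD continuously".

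The same section sets out when lost dosing is itself a DLT:
- Delay, automatic: "Any toxicity causing greater than 2 weeks of dose delay of either PF-07248144" (partner agent redacted) is a DLT.
- Delay, discretionary: clinically important or persistent toxicities, with the example "toxicities responsible for significant dose delay) that are not included in the above criteria may also be considered a DLT following review" by investigators and sponsor. No number of days is given.
- Reduction, automatic: a dose reduction "due to a treatment-related AE (per protocol) during the first 28 days will be qualified as participant experiencing DLT".

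Grade 3 or higher related non-hematologic events are DLTs, with listed clarifications. Isolated Grade 3 neutropenia is expressly not one.

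Section 9.4.1 determines the MTD on the per protocol set. Section 9.3 (repeated in SAP section 3) admits to that set treated participants who had a DLT or had no major treatment deviation in the observation period. The 75% rule is not mentioned there. Section 9.4.1 also plans a sensitivity analysis that "uses weighted DLT/AE data (in equivocal cases) into the BLRM model estimation".

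**The concern.** The evaluability rule and the automatic delay rule use thresholds that do not meet. A participant whose dosing is held for toxicity for longer than the first tolerates, but not long enough for the second, can leave the DLT denominator because of the outcome the escalation is meant to measure, and a newly enrolled participant can take the place.

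The dose decision under 4.3.4 depends on the posterior probability that the DLT rate lies in the overdosing interval, with a cap of 25%. Cohorts are about three participants, so the handling of a single person can decide whether a dose may be used.

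The situation is plausible for this drug. Section 2.2.4 reports Grade 3 or higher treatment-related neutropenia in 17 of 59 participants (28.8%), the most frequent severe related event. Section 6.6.1 provides for toxicity interruptions and for resumption within 4 weeks, and does not make up omitted doses in the cycle. The rule still matters, because Amendment 4 adds a further combination escalation.

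**Working it through.** **Step 1: the band.** Inputs: once-daily dosing (Table 1), 28 days and 75% (4.3.5), delay over two weeks (4.3.5). Planned doses are 28 and the minimum is 0.75 × 28 = 21. For one continuous toxicity hold:

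| Doses missed | Received | DLT-evaluable without a DLT? | Automatic DLT by delay? |
|---|---|---|---|
| 7 | 21/28 = 75.0% | yes | no |
| 8 | 20/28 = 71.4% | no | no |
| 14 | 14/28 = 50.0% | no | no (not over two weeks) |
| 15 | 13/28 = 46.4% | yes, through the DLT | yes |

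The band is 8 to 14 missed doses. For example, a hold on Days 10 to 20 with restart at the same dose misses 11 doses and leaves 17/28 = 60.7%.

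**Step 2: what takes a participant out of the band.** A Grade 3 or higher related non-hematologic event, another listed criterion, or a treatment-related dose reduction by Day 28 makes the case a DLT. The review clause can do so but need not. What remains is a hold for an unlisted toxicity, with no reduction in the window, that reviewers do not call a DLT. Isolated Grade 3 neutropenia with a same-dose restart fits this.

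**Step 3: the MTD set.** Whether an interruption provided for in 6.6.1 is a major treatment deviation is not stated in 9.3. If it is, the participant is excluded. If it is not, the participant enters as a full non-DLT on as little as 50% of the doses. Neither reading counts the failure to take the dose against that dose.

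**Step 4: direction.** Let d be the rate of DLTs as defined and g the rate of holds in the band, both assumed. The modelled rate is d if holds enter as non-DLTs, d/(1 − g) if they are dropped, and d + g if they are counted as DLTs. With d = 0.20 and g = 0.10 these are 0.20, 0.20/0.90 = 0.222 and 0.30. Dropped minus counted equals −g[1 − d/(1 − g)]. Over d from 0.10 to 0.33 and g from 0.05 to 0.20, the shortfall runs from 0.05 × (1 − 0.33/0.95) = 0.033 to 0.20 × (1 − 0.10/0.80) = 0.175.

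**Step 5: effect on one decision.** The prior details in Appendix 9 are redacted, so the protocol's model cannot be rebuilt. As a stand-in, take a single dose with x DLTs in n participants, posterior Beta(a + x, b + n − x), and Pr(rate > 0.33). Assume six treated, one DLT and one hold in the band.

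| Handling of the hold | x/n | Jeffreys (0.5, 0.5) | Assumed Beta(0.4, 1.6) |
|---|---|---|---|
| Replaced by a non-DLT, or entered as one | 1/6 | 0.204 | 0.125 |
| Dropped, not replaced | 1/5 | 0.285 | 0.178 |
| Counted as a DLT | 2/6 | 0.528 | 0.390 |

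Under both priors the first and last rows lie on opposite sides of 25%.

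**The case against.** The strongest objection concerns direction. EWOC and the 0.33 boundary apply to the DLT rate as the protocol defines it. With d = 0.20 and g = 0.15, dropping holds raises the modelled rate to 0.20/0.85 = 0.235, which is more cautious than entering them as non-DLTs. A reader might infer that the rule simply biases toward escalation, or might add DLTs and holds together and set the sum against 0.33. The documents support neither: toxicity is understated only relative to counting holds wholly or partly as DLTs, and the sum is a different quantity from the one the boundary is set on. This stands and limits the claim.

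A reader might also infer that a hold starting in the second half of the cycle can never become a DLT. Section 4.3.5 does not say that the delay must finish within 28 days, and it lets DLT-type events after the window inform escalation and the MTD/RDE. That inference fails.

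Other points reduce the weight without closing the gap:
- The review and dose-reduction clauses catch some cases. All three reported DLTs were Grade 3 neutropenia (2.2.4), which fits with that, although the route is not stated.
- Replacement is optional, and exclusion from the MTD set is possible but not stated.
- The 17/59 pools escalation and expansion, is not limited to Cycle 1 and gives no hold durations.
- Safety discussions include participants not applicable for DLT assessment (9.6), and the RDE may be set below the MTD (4.3.7).
- Weights for equivocal cases may be specified in the redacted part of Appendix 9, so they cannot be called absent. The visible text does not say that these participants qualify.
- The monotherapy and fulvestrant RDEs are already identified (2.2.4), so the reach is the remaining combination escalation.

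**Conclusion.** The point holds in a limited form. A participant who misses 8 to 14 of 28 doses because of toxicity, with no listed criterion met and no dose reduction in the window, is not automatically a DLT, is not DLT-evaluable, and may be replaced without regard to the reason. Section 9.3 does not settle whether that participant is excluded from the MTD set or enters as a full non-DLT. The handling of a toxicity-driven outcome is left to case-by-case judgment in an open-label escalation.

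The band is exact arithmetic from the stated rules. The size of the effect is not known, because the documents give no Cycle 1 hold rate. The figures in steps 4 and 5 rest on assumed rates, priors and counts, and show only that one such participant can move a result across the 25% cap. This is a cheap improvement worth making before the remaining combination cohorts, not evidence that any past dose decision was wrong.

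**What to change.** Reconcile the evaluability rule and the delay rule in Protocol 4.3.5 with the per protocol set in 9.3, and carry the same text into SAP section 3:

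1. Allow replacement for receiving less than 75% of doses only when the doses were missed for reasons unrelated to treatment.
2. Keep participants below 75% because of treatment-related toxicity in the MTD analysis set, and do not replace them.
3. Send each such case through the existing DLT review clause. Where it remains equivocal, use the existing weighted analysis in 9.4.1, with the weight set before the cohort's data are reviewed.
4. At each dose decision, show the BLRM overdose probability with and without these participants.

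No clinical threshold changes. The cost is a few sentences and one extra model run per decision. The downside is slightly more cautious escalation in the remaining combination cohorts.
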